# Rational and aim of the study

Current chemotherapy for advanced non-small cell lung cancer, not amenable for curative local treatment (surgery or chemoradiotherapy), has a modest life-prolonging effect and can improve quality of life. There is however no potential for long-term cure for these patients.

Chemotherapy also produces variable and often significant toxicity.

Current retrospective evidence suggests that significant clinical responses can be obtained when patients whose cancer cells have an EGFR TKD mutation are treated with an EGFR TKI.

The ease of administration and toxicity profile of TKI compare favourably with that of chemotherapy, even single agents such as for example gemcitabine

The present study will establish the clinical benefit rate of TKI as a first line treatment in patients with EGFR mutations and thus estimate the proportion of patients who might benefit for a prolonged period from a treatment with a modest toxicity profile.

# Study objectives and endpoints

## Primary objective and primary endpoint

Establish clinical benefit (progression free survival) of first line RTKI in patients with stage IV and stage IIIB NSCLC not eligible for curative-intent treatment (chemo-radiotherapy) carrying a mutant EGFR-1.

## Secondary objectives and secondary endpoints

- - Determine response rate (OR and stable disease) and duration under erlotinib treatment.
- Determine the effect on Quality of Life (QOL) of first-line anti-EGFR-1 treatment.
- Determine the value of positron emission tomography (PET)-scan as an early predictor of response and clinical benefit.
- Overall survival from the time of study entry to the date of death or date of last follow-up.
- Determine biological correlates for response/resistance in tumour tissues.

# Patient selection criteria

## Criteria for inclusion in the study

- Histological or cytological documented diagnosis of inoperable, locally advanced, recurrent or metastatic (Stage IIIB or Stage IV) adenocarcinoma of the lung in a patient with a smoking history of < 15 years and quit smoking > 1 year before diagnosis.
- Patients must have evidence of disease but measurable disease is not mandatory.
- 18 years of age or older.
- ECOG performance status of 0 – 3.
- Patients not eligible for standard curative-intent treatment with surgery or chemo-radiotherapy.
- Life expectancy  3 months.
- Prior therapy for NSCLC allowed for primary disease: surgery and radiotherapy and adjuvant or proto-adjuvant chemotherapy completed > 6 months before inclusion
- Adequate bone marrow, hepatic and renal function:
  - Granulocyte count > 1.5 x 109/L and platelet count > 100 x 109/L
  - Serum bilirubin must be < 1.5 upper limit of normal (ULN).
  - If alkaline phosphatase is > 2.5 x ULN, SGOT (AST) and SGPT (ALT) must be < 1.5 x ULN.
  - Serum creatinine < 1.5 ULN or creatinine clearance > 60 ml/min.
- Ability for giving informed consent for participating in the study and filling out FACT-L quality of life scales.
- Able to comply with study and follow-up procedures.
- Availability of tumour biopsy sample (fixed in formalin and, if possible, also snap frozen tumour sample). If frozen samples are available, these will be collected by central data management.
- Informed Consent for performing mutation analysis and subsequent biomarker analysis.
- Separate signed Informed Consent for participation in the treatment phase of the study.
- Ability to take oral medication.
- For all females of childbearing potential a negative pregnancy test must be obtained within 48 hours before starting therapy.
- Patients with reproductive potential must use effective contraception.

## Criteria for exclusion

- Patients with previously untreated disease for whom urgent chemotherapy or radiotherapy is deemed necessary (e.g. rapidly progressive disease).
- Absence of tumour biopsy material available for mutation analysis.
- Current symptomatic central nervous disorder, brain or leptomeningeal metastasis. Previously diagnosed and treated CNS metastases or spinal cord compression with evidence of stable disease (clinically stable imaging) for at least 2 months is permitted.
- Pre-existing symptomatic interstitial lung disease, not related to the current malignancy.
- Patients with a history of other malignancies, except patients with basal cell carcinoma of the skin or in situ carcinoma of the cervix with a disease free interval of  5 years. Patients with a prior history of other good prognosis malignancies more than 5 years since end of treatment and in un-maintained complete remission also can be considered for inclusion after discussion with the Principal Investigator
- Prior therapy with systemic anti-tumour therapy with HER1/EGFR inhibitors (small molecule or monoclonal antibody).
- Prior chemotherapy for metastatic disease.
- Concomitant treatment with corticosteroids, except chronic treatment lasting more than one month, at low dose ( 20mg of methylprednisolone or equivalent per day).
- Significant malabsorption syndrome or disease affecting the gastrointestinal tract function
- Pregnant or breast-feeding women; for women in reproductive condition, a negative pregnancy test is required.
- Male or female patients with reproductive potential who do not use an approved contraceptive method during and for 3 months after the end of the treatment.
- Concomitant food or drug intake which potentially impairs absorption and metabolisation of RTKI's.
- Psychological, familial, sociological or geographical conditions potentially compromising compliance with the study protocol and follow up schedule.
- Participation in another clinical trial with any investigational drug within 30 days prior to study screening.
- Any unstable systemic disease (including active infection, grade 4 hypertension, unstable angina, congestive heart failure, hepatic, renal or metabolic disease).
- Any significant ophthalmological abnormality, especially severe dry eye syndrome, keratoconjunctivitis sicca, Sjögren syndrome, severe exposure keratitis or any other disorder likely to increase the risk of corneal epithelial lesions. The use of contact lenses is not recommended during the study. The decision to continue to wear contact lenses should be discussed with the patient’s treating oncologist and ophthalmologist.
- Nursing mothers.

## Concomitant Medication

- Patients who have evidence of disease progression requiring radiation therapy should discontinue protocol treatment.
- Patients should receive full supportive care per institutional standards.
- Concomitant biphosphonate use to control bone pain is permitted.
- Patients with dry eyes (an abnormal Schirmer’s test results on baseline eye exam) should be advised to use an ocular lubricant.
- Concomitant treatment with warfarin or coumarin-derivative is permitted provided increased vigilance occurs with respect to monitoring INR.
- Administration of any other anti-cancer therapy (cytotoxic, biological/immunotherapy or full dose radiotherapy) is not permitted until after disease progression is documented. After permanently discontinuing the protocol treatment, patients may be treated at the investigators discretion.
- Patients who receive protocol treatment should not receive ANY other (non-anticancer) investigational drugs until after the post-treatment assessment (at least 30 days after the final dose of protocol treatment).
- Patients who continue to wear contact lenses may have an increased risk of ocular adverse events. The decision to continue to wear contact lenses should be discussed with the patient’s treating oncologist and ophthalmologist.

**Potential for Drug Interactions.**

Substances that are potent inhibitors of CYP3A4 activity (eg, ketoconazole) decrease erlotinib metabolism and increase erlotinib plasma concentrations. This increase may be clinically relevant as adverse experiences are related to dose and exposure; therefore, caution should be used when administering CYP3A4 inhibitors with erlotinib.

Substances that are potent inducers of CYP3A4 activity (eg, rifampin, phenytoin) increase erlotinib metabolism and significantly decrease plasma concentrations. This decrease in exposure may be clinically relevant, as preclinical studies suggest that higher concentrations are more efficacious in in vivo animal tumour models. However, the relationship between exposure and efficacy in cancer patients has not been adequately studied. See Appendix 4: CYP3A4 Inhibitors.

International Normalized Ratio (INR) elevations and/or bleeding events have been reported in some cancer patients taking warfarin while on erlotinib. Patients taking warfarin or other coumarin-derivative anticoagulants should be monitored regularly for changes in prothrombin time or INR.

# Study design and conduct.

Patients diagnosed with advanced non-small cell lung cancer and meeting the selection criteria can be considered for study inclusion. Patients concomitantly receive the Informed Consent form for mutation analysis of their tumor material and the Informed Consent for the treatment phase of the study. The Informed Consent for the mutation analysis includes the possibility for a repeat biopsy if the available material is insufficient and a biopsy is possible and safe. It also includes the possibility of performing a second biopsy (if possible and safe) upon progression under protocol treatment for study of secondary resistance mechanism. After obtaining both consents, the baseline examinations needed for the study can be performed in parallel to the mutation analysis, the result of which should be available within 2 weeks. Patients will be included in the study after filing of the inclusion form with the central data management and principle investigator. Eligibility for subsequent protocol treatment depends on the identification of a kinase domain mutation in the TK domain of the EGFR.

The maximal interval allowed between baseline exams and initiation of study is 3 weeks.

After documentation of unequivocal objective progression the patients will go off study. If the patient leaves the study because of unacceptable toxicity or any other reason without progressive disease, the assessments for determination of response duration will continue until disease progression is documented.

### **Summary of study flow.**

### Tumour biopsy for diagnosis and EGFR mutation analysis.

### In view of the time needed to perform the mutation analysis, it is preferable (but not mandatory) to obtain this sample at the time of the initial diagnosis.

### Separate Informed Consents for mutation analysis and participation in the study.

### Baseline evaluation, during which the mutation screen is being performed.

### Evaluation of eligibility.

### Inclusion and treatment.

### Response assessments (imaging and physical) and ancillary parameters at 6, 12, 18 and 24 weeks. Thereafter every 12 weeks until disease progression (RECIST definition). A first metabolic response assessment will be at 2 weeks and subsequently synchronized with the radiological evaluations. A concomitant CT-scan at 2 weeks is recommended.

### Patients remain in study until disease progression/unacceptable toxicity.

# Response Assessments

## Radiological assessments.

Up to a maximum of five measurable lesions for each site are identified as target lesions and measured at baseline. The sum of the longest diameter for all target lesions will be calculated and reported as the baseline sum longest diameter, which will be the reference to evaluate the tumor response to treatment. The same method of assessment and the same technique should be used to characterize each identified and reported lesion at baseline and during follow-up.

Other lesions should be identified as non-target lesions and should also be recorded, but not measured, at baseline. They should be followed as “present” or “absent”.

Patients without measurable lesions will be scored for disease progression, also according to Recist criteria.

RECIST (Uni-dimensional Tumour Measurement) will be used to evaluate best response during the treatment by the local investigator (23).

Confirmation of responses (CR, PR) has to be performed at least 4 weeks after initial documentation, in practice it will normally coincide with the next scheduled 6-weekly evaluation.

Evidence of progression will be reviewed by the local investigator and the principal investigator before ending erlotinib treatment. All responses will also be reviewed at the end of the study centrally in collaboration with the writing committee of the study.

Each subject will be assigned a best objective response as per investigators decision (according to RECIST criteria, see Appendix 2). This is defined as the best response recorded from the start of treatment until disease progression/recurrence. Objective response will be summarized in a descriptive manner.

## Metabolic assessment.

The PET-scan imaging with FDG will be performed at baseline, at day 14 and at 6 weeks and 12 weeks. The evaluation of the PET-scan at 2 weeks is essential for assessing the predictive value of PET imaging for radiological response determination. The PET-scan will in no instance be used to make decisions about continuation or discontinuation of the experimental treatment, which only relays on the radiological and clinical assessments. The continuation of repeat PET-scan at week 12 and subsequent assessments will be in consultation with [name], [name] and the Principal Investigator on a case-by-case basis. The PET acquisition protocol should be as simple as possible (WB-FDG with AC). The protocol should be according to local standards but standardized: For each patient the same camera should be used, similar at the G-dose, glucose measurement and same acquisition and reconstruction protocol. The scan should start 60 to 90 minutes post injection.

PET data analysis. Quantitative PET analysis

- SUV max, glucose correction + largest metabolic lesion diameter. Local reading and recorded in CRF. EORTC PET criteria will be applied for metabolic response determination: up to 5 target lesions (diameter > 2 cm). The target lesions for PET and radiological imaging can be different. Metabolic complete response is complete normalisation of FDG uptake, metabolic partial remission is 25% decrease, SUV max. in all target lesions, metabolic progressive disease is 25% increase, SUV max. in one target lesion or 25% increase in lesion diameter if one target or appearance of no lesions. Metabolic stable disease is all other.

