### Schedule of Assessments

Table 4.

|  | **Screening/**  **Baseline**  **Maximum days prior to first treatment** | **Treatment Period**  **Timing** | **End of Study** |
| --- | --- | --- | --- |
| Informed Consent | 3 weeks | - | - |
| Demographics | 3 weeks | - | - |
| Medical history | 3 weeks | - | - |
| Physical examination | 3 weeks | Every 6 weeks | X |
| Pregnancy test1 | 48 hours before starting erlotinib | - | - |
| Laboratory2 | 2 weeks | Every 6 weeks | X |
| Tumor measurements3 | 2 weeks | - On day 14.  - Then every 6 weeks from treatment initiation, up to 6 months of follow-up  - Thereafter q 12 weeks | X |
| Tumor Biopsy and mutation analysis 4 | pretreatment |  |  |
| ECOG Performance Status | 7 days | Every 6 weeks | X |
| erlotinib administration |  | Continuously | - |
| Safety5 | - | Recorded throughout study | X |
| Survival | - | - | X |

1. In women of childbearing potential only
2. Hematology: Hemoglobin, WBC, granulocytes and platelet count, INR (Only for patients receiving warfarin or coumadin-derivative. To be done twice per week during for 3 weeks; then weekly or more often as clinically indicated.) Biochemistry: Alkaline phosphatase, Serum bilirubin, Serum creatinine, AST (SGOT) and ALT (SGPT). Only laboratory abnormalities linked to unexpected clinical symptoms will be documented in the CRF.
3. CT scans, MRI or X-ray as per Institutional Standards and FDG-scan (appendix 5 for CT-scan and FDG-scan specification). The first FDG scan is at day 14. It is also proposed that a CT-scan is performed at the same time point.
   For responding patients, a confirmatory evaluation should be repeated at least 4 weeks (normally at the next 6 week interval evaluation) after the initial determination of response.
4. A formaline fixed paraffin tissue block representative of the patient's primary cancer at the initial diagnosis or a pretreatment bronchoscopy biopsy or a biopsy from a metastatic site will be sent to the Laboratory of Molecular Oncology, Oncology Centre, AZ-VUB.
5. Serious Adverse Events, Adverse Events leading to premature withdrawal, unexpected erlotinib related AEs and erlotinib related rash.

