### PET-scan for evaluation of metabolic response

Patient preparation

- 6 hours fasting (postpone patient if not fasted)
- valium p.o. prophylaxis if needed
- diabetes patients under peroral treatment: overnight fasting; no peroral antidiabetics in the morning; plan patient early in morning; if glycemia > 140 and < 200 mg%  follow scheme here under.
- in insuline-dependent diabetes patients: plan patient early in the morning after overnight fasting; no insuline in the morning.

-if fasting glycemia < 140 mg%  FDG injection;

-if fasting glycemia > 200 mg/dl:  exclude patient

-if > 140 mg/dl et < 200 mg/dl  administration of IV Insuline and monitor glycemia until under 140 mg%.

Image acquisition

- start imaging at 60 minutes (+/- 5 minutes) post FDG administration
- whole body post-injection transmission scan or, CT (in case of PET-CT camera) for attenuation correction
- note body weight / length / glycemia

Image analysis

- visual analysis: 3 points score: normal, equivocal, pathological
- response analysis (always in relation to the baseline, pre-treatment, PET-imaging): 4 points score according to the criteria defined by the EORTC PET study group for assessing response using FDG18
  - Progressive metabolic disease
    - Increase in SUV of more than 25%
    - Visual increase in lesion extent (>20% in longest dimension)
    - New metastatic lesions
  - Stable metabolic disease
    - Increase in SUV < 25%, decrease < 15%
    - No visible increase in the extent of FDG uptake
  - Partial metabolic response
    - Reduction in SUV between 15 and 25% after 1 cycle of treatment
    - Reduction in SUV > 25% after more than 1 cycle of treatment
  - Complete metabolic response
    - Complete resolution of FDG-uptake

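### Section 9.2 and Appendix 5 give conflicting metabolic response rules, so one FDG-PET scan can fall into different classes

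*Protocol*

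**What the plan says.** Section 9.2 (Metabolic assessment) and Appendix 5 (PET-scan for evaluation of metabolic response) both claim to apply the EORTC PET criteria.

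- **Partial response.** Section 9.2: "metabolic partial remission is 25% decrease, SUV max. in all target lesions", whatever the time point. Appendix 5 has two rules: "Reduction in SUV between 15 and 25% after 1 cycle of treatment" and "Reduction in SUV > 25% after more than 1 cycle of treatment". It names neither SUVmax nor a requirement that every target lesion respond.
- **Stable disease.** Section 9.2: "Metabolic stable disease is all other". Appendix 5 limits it to a rise under 25% or a fall under 15%.
- **Progression by size or new disease.** Section 9.2: "25% increase in lesion diameter if one target or appearance of no lesions". Appendix 5 uses a visual increase in extent above 20% of the longest dimension, or new metastatic lesions.
- **Uptake time.** Section 9.2: "The scan should start 60 to 90 minutes post injection". Appendix 5: "start imaging at 60 minutes (+/- 5 minutes) post FDG administration".

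Section 6.2 makes the value of PET as an early predictor a secondary objective. The synopsis lists metabolic response rate among the secondary objectives. Section 9.2 calls the two-week scan essential for the predictor question. Scans are read locally and entered in the CRF.

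**The concern.** A local reader with a day-14 scan has two rule sets and no statement of which takes precedence. The Appendix 5 rules also depend on counting cycles. Erlotinib is one oral dose a day without interruption (Section 11.4 and Table 4), and the protocol defines no cycle length. Section 12.6 mentions a last treatment cycle but does not say what a cycle is.

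The trial is multicentre, so sites may classify by different rules and the pooled classes would not mean the same thing. At stake are the metabolic response rate and any measure of how well day-14 PET predicts radiological response or clinical benefit. The protocol has fixed the definition twice, incompatibly, so this is not detail left to an analysis plan.

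**Working it through.** There is no planned figure to reproduce. The check applies each text literally to the same scan. Inputs are the class limits in Section 9.2 and Appendix 5. Appendix 5 is read both ways, because the protocol does not say whether day 14 is one cycle or more than one.

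**Step 1. SUV change from baseline at day 14, single target lesion, no change in size, no new lesion**

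| SUV change | Section 9.2 | Appendix 5, day 14 as one cycle | Appendix 5, day 14 as more than one cycle |
|---|---|---|---|
| Complete normalisation | complete | complete | complete |
| −40% or −30% | partial | no class (literal) | partial |
| −25% exactly | partial | partial | no class |
| −20%, −16% or −15% | stable | partial | no class |
| −10%, 0%, +10% or +24% | stable | stable | stable |
| +30% | progressive | progressive | progressive |

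The texts agree on complete normalisation, on falls under 15%, on rises under 25% and on rises clearly above 25%. They disagree for falls of 15% to under 25% on either reading of cycle. For larger falls short of normalisation they disagree only if day 14 is one cycle and Appendix 5 is read literally.

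**Step 2. Increase in lesion size, SUV unchanged**

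| Increase | Section 9.2 (25% in diameter) | Appendix 5 (above 20% in longest dimension) |
|---|---|---|
| 15% | stable | stable |
| 22% | stable | progressive |
| 26% | progressive | progressive |

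The conflict covers increases above 20% and below 25%.

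**Step 3. More than one lesion.** Take two target lesions, one falling 30% and the other 10%. Section 9.2 requires the fall in every target lesion, so the patient is stable. Appendix 5 does not say which lesion or which SUV measure counts, so its class cannot be determined from the text.

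**Step 4. New disease.** Taken literally, Section 9.2 makes the appearance of no lesions a sign of progression. Appendix 5 has new lesions, so this is evidently a slip for new.

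**Step 5. Uptake window.** Appendix 5 allows 60 − 5 = 55 to 60 + 5 = 65 minutes, and Section 9.2 allows 60 to 90. The windows share only 60 to 65 minutes. A start at 57 minutes meets Appendix 5 only, and a start at 80 minutes meets Section 9.2 only.

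**The case against.** **The predictor is not lost.** Section 9.2 has SUVmax and the largest metabolic lesion diameter recorded in the CRF, so one rule can be applied to all patients at analysis. This stands for most of the classification and limits the harm. It does not settle which rule to apply, and it cannot change the uptake time of a scan already acquired. Section 9.2 does require the same camera and acquisition protocol within a patient, which limits the effect of uptake time on within-patient change.

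**The gap for falls above 25% after one cycle is hyper-literal.** A sensible reader would take the 15–25% band as a minimum and call a 40% fall a partial response. This is fair. The conflict for falls of 15% to under 25% remains.

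**PET does not guide care.** Section 9.2 says PET is never used to continue or stop treatment. This stands, so neither conduct nor the primary endpoint is touched.

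**A stronger reading is tempting in Table 4.** Note 3 says "The first FDG scan is at day 14", and a reader might infer that baseline scans are omitted and patients cannot be scored. The documents do not support that. Sections 9.2 and 13 both schedule a baseline FDG-PET, and the Table 4 row carrying the note has a baseline entry. The summary of study flow in Section 8 places the first metabolic response assessment at two weeks, which explains the word first. The note is loose wording for the first on-treatment scan.

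**A reader might also want a count of affected patients** or a shift in sensitivity and specificity. The protocol gives no distribution of day-14 SUV change and no split of responders, so any such figure would rest entirely on assumption. None is offered here.

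**Conclusion.** The concern holds as a contradiction in current text. Under the same EORTC label, Section 9.2 and Appendix 5 give different classes for falls of 15% to under 25% and for size increases above 20% and below 25%. They also differ on which lesions must respond and on the uptake window. The cycle-based thresholds cannot be applied to continuous daily dosing without a definition that the protocol does not give.

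The size is limited. Only the stated bands are affected, not every patient, and only the secondary PET objectives. Most classes can be re-derived if SUVmax and diameters are recorded as Section 9.2 requires. The conclusion rests on the wording alone and needs no assumed distribution. It should be corrected, but it does not threaten the main result. A statistical analysis plan, not seen here, might choose one rule for analysis, but local readers and scan timing follow the protocol.

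**What to change.** Reconcile Section 9.2 and Appendix 5 into one definition and have the other place refer to it. The definition should:

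- be tied to the scan time points (day 14, week 6, week 12) instead of cycles;
- use exhaustive, non-overlapping SUV bands with the boundary values assigned;
- name the SUV measure and say which lesions must meet the threshold;
- give one size threshold for progression, and say new lesions where Section 9.2 says no lesions;
- give one uptake window.

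Apply that definition to all recorded SUVmax values and diameters at analysis, so that locally assigned classes do not mix rules. The choice of thresholds and window is for the sponsor and its PET experts. As a minor wording correction, Table 4 note 3 should say that day 14 is the first on-treatment FDG scan, after the baseline scan already scheduled in Sections 9.2 and 13.

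The cost is text edits in three places, plus re-deriving the class of any scan already read. No scan is added and patient care does not change.
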